### Data management and specimen banking

Collected breast milk and stool samples will be labelled with a four digit number randomly assigned to each patient as well as the date of sample collection. De-identified samples will be delivered to the laboratory for processing. Precautions will be taken to maintain the privacy of all participants. Personal information maintained on infant subjects will include age, first initial, last name, and four digit medical record number assigned at the time of randomisation. Patient information will not be disclosed to third party individuals except those authorised to oversee the research project.

## Study endpoints

### Primary outcome measures

#### *Identification of pharmacologically effective dose (ED) of* B. infantis

The primary endpoint of the study is identification of the ED of *B. infantis*, i.e. the dose required to produce predominant (>50 %) gut colonisation at 6 weeks of age. The value of 50 % colonisation was chosen because *B. infantis* represented greater than 50 % of the gut microbiota in the vast majority of Bangladesh infants [19]. The percent gut colonisation will be determined through analysis of stool samples by 16S sequencing.

#### Safety

An additional primary endpoint is to determine the safety of *B. infantis* supplementation in immunocompetent, full-term infants. Any adverse events including fever of 38.9 °C (102 °F) or higher, abdominal pain or colic, blood or purulence in the stool, diarrhoea or vomiting will be documented and dosing adjusted accordingly (“Stopping rules” are defined below).

### Secondary outcome measures

#### Milk oligosaccharide consumption

All stool samples will also be analyzed for the presence of oligosaccharides unique to breast milk and for the presence of free saccharide monomers, which are products of their incomplete digestion. *B. infantis* abundance will be correlated to these values.

#### Microbiota composition

In addition to determining the percent composition of *B. infantis* in infant stool samples, numerous other measures such as microbiota diversity (Shannon Diversity plots) and rate of *B. infantis* decline following cessation of breast feeding will also be determined.

### Provisions to monitor data and ensure safety of subjects

Children will be recruited for this study. Subjects will be monitored clinically during the study period to assess for potential adverse events. A previous study of *B. infantis* supplementation in premature infants administered similar doses and was well tolerated with no severe adverse events noted [22]. Nonetheless, patients enrolled in the study will be monitored closely and any evidence of feeding intolerance, illness, or infection will be thoroughly evaluated. A survey to assess for any baseline feeding intolerance or symptoms will be administered to all infants prior to administration of *B. infantis* or placebo. Additional symptom questionnaires will be administered weekly during the first month of the study and at every study visit therafter at 6, 24, 36, 52, and 78 weeks. Patients will be provided with the contact information for the principal investigator and on-call dermatology resident should any unforeseen symptoms or problems arise.

### Rules for stopping dose escalation and halting trial

Dose escalation will be stopped if a maximally tolerated dose (MTD) of *B. infantis* is reached. The data safety monitoring board will evaluate the adverse events reported at each ascending dose of *B. infantis*. If the safety monitoring board deems that one or more of the three infants in the *B. infantis* supplementation group experienced an adverse event (such as fever >38.9 °C (102 °F), abdominal pain or colic, blood or purulence in the stool, diarrhoea or vomiting) then additional dose escalation will be halted.In the event dose escalation is halted due to adverse events, an additional group of five infants will be enrolled with three infants at the same (i.e. not escalated) dose of *B. infantis* and two receiving placebo.If no adverse events occur in this additional, non-escalated group, then dose escalation will be resumed beginning with the next group of enrolled infants.However, if adverse events are noted in one or more infant(s) in the non-escalated group, all further dose escalation will be halted. The *B. infantis* dose will be de-escalated to the previous value, and an additional group of five infants (three *B. infantis*, two placebo) will be enrolled. If no adverse events occur in the de-escalated group, this dose will be considered the MTD and the trial will be stopped.If any adverse events are noted in the de-escalated group, further de-escalation and enrollment of infants will occur to identify the dose of *B. infantis* considered to be the MTD, in which no adverse events occur in the study group.

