### Study-wide number of subjects

We propose a maximum sample size of 90 infants. Five infants (three to receive *B. infantis* supplementation and two to receive placebo) will be enrolled for the initial dose of *B. infantis*. An additional five infants will be enrolled at each dose escalation. Once the pharmacologically effective dose (ED) of *B. infantis* has been reached, two additional dose escalations will be performed (for reasons as described above). We estimate that the ED of *B. infantis* will be identified within seven dose escalations (35 infants). Accounting for the final two dose escalations will bring the total to 45 infants. Following the final dose escalation, 45 additional infants (27 to receive *B. infantis* and 18 to receive placebo) will be enrolled to screen for lower-frequency adverse events using Hanley’s Rule of Three [21]. This will bring the maximum enrollment number to 90 infants. If the ED of *B. infantis* required to produce 50 % gut colonisation at 6 weeks is not reached, then enrollment will be halted after 90 infants have been enrolled. Additional stopping rules are listed in the “Study Endpoints” section.

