## Discussion

From our experience of administering *B. infantis* to infants in the NICU at UC Davis, it is highly unlikely that a phase I trial will successfully identify a MTD of this probiotic. Thus, our proposed phase I ascending dose study will instead utilise a targeted outcome, optimal gut colonisation of *B. infantis* at 6 weeks of age. Such “concentration controlled” phase I clinical trials that use pharmacokinetics in place of drug toxicity to guide dose escalation are supported in the literature [23, 24]. For example, in molecularly targeted anticancer agents, toxicity concerns are reduced, making “drug-related biological effects” a better suited primary endpoint [25–28]. Our specific trial will measure gut microbiota composition following *B. infantis* administration to determine the dose of *B. infantis* that is required to successfully colonise the gastrointestinal tract of a 6-week-old breastfed infant. Secondary outcome measures will include measurement of complex glycan consumption by the infant as well as diversity of the intestinal microbiota. As in all phase I studies, the infants will be monitored closely for adverse events. The main goal of this phase I trial is to establish a recommended administering dose of *B. infantis* to support further efficacy testing in phase II and phase III trials.

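### After the first halting trigger, the stopping rule no longer says that only *B. infantis* infants count, so a placebo-only event can, read literally, confirm a halt or force de-escalation

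*Protocol article*

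**What the plan says.** All of the relevant text is in the protocol article under Rules for stopping dose escalation and halting trial.

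- **First trigger.** It names the arm. The condition begins "If the safety monitoring board deems that one or more of the three infants in the" and goes on to specify the *B. infantis* supplementation group.
- **Repeat group.** After a first trigger, "an additional group of five infants will be enrolled with three infants at the same (i.e. not escalated) dose of" *B. infantis*, and the sentence adds two infants on placebo.
- **All-clear for the repeat group.** "If no adverse events occur in this additional, non-escalated group, then dose escalation will be resumed". No arm is named.
- **Repeat-group trigger.** "However, if adverse events are noted in one or more infant(s) in the non-escalated group, all further dose escalation will be halted". No arm is named. The dose is then lowered one step and another five infants are enrolled, three on *B. infantis* and two on placebo.
- **De-escalation trigger.** "If any adverse events are noted in the de-escalated group, further de-escalation and enrollment of infants will occur". No arm is named.
- **MTD definition.** The dose "considered to be the MTD, in which no adverse events occur in the study group". The term for the group is not defined.

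The qualifying events include colic, diarrhoea and vomiting, with no grade or causality requirement stated. The Discussion says that "it is highly unlikely that a phase I trial will successfully identify a MTD of this probiotic". The Study-wide number of subjects section expects the effective dose (ED) to be found within seven dose groups of five.

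**The concern.** An event in a placebo infant says nothing about whether a *B. infantis* dose is tolerated. The first trigger respects this. The later ones, on their wording, do not, and they carry the heavier consequences: a permanent end to escalation, and a forced step down. The sponsor expects no MTD to be found, so its own expected case is that most triggers are background illness, which placebo infants have as well.

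A permanent halt costs the primary endpoint only if the ED lies above the doses already given. Short of that, the ambiguity itself matters: two boards with the same data at the same dose could act in opposite ways, one resuming escalation and the other ending it.

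**Working it through.** **Reading the text.** The all-clear for the repeat group uses a demonstrative that points back to the group just introduced, which has five infants including two on placebo. Study design and Study-wide number of subjects also describe enrolment in groups of five. The literal reading is therefore a natural one. Nothing in the article limits the later triggers to *B. infantis* infants.

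**Order of events.** The repeat group exists only if a *B. infantis* infant at that dose has already had an event. A placebo event can therefore turn a temporary pause into a permanent halt, but cannot cause the pause.

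**Inputs.** Three *B. infantis* and two placebo infants per group (article). The article gives no operating characteristic for the rule, so there is no stated figure to reproduce. The chance p that an infant has a listed event in the review window is not given; it is assumed to lie between 2% and 40%, equal in both arms (no product effect), with infants independent. Seven levels is the sponsor's upper estimate for reaching the ED; four levels illustrates an earlier ED.

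**Formulas.**

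- Trigger when only the three active infants count: q3 = 1 − (1 − p)^3.
- Trigger when all five count: q5 = 1 − (1 − p)^5.
- Repeat-group trigger from placebo infants alone: (1 − p)^3 × [1 − (1 − p)^2] = q5 − q3.
- Permanent halt at one level: h = q3 × q3 (active only) or h = q3 × q5 (literal).
- Permanent halt within L levels: 1 − (1 − h)^L.

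**Example, p = 10%.** q3 = 1 − 0.9^3 = 0.271 and q5 = 1 − 0.9^5 = 0.410. Placebo infants alone account for 0.139 of the 0.410, or 34% of repeat-group triggers. h = 0.271 × 0.271 = 0.073 (active only) or 0.271 × 0.410 = 0.111 (literal). Over seven levels: 1 − 0.927^7 ≈ 0.41 against 1 − 0.889^7 ≈ 0.56, a difference of about 15 points.

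| p | q3 | q5 | Halt in 7 levels: active only → literal | Added (points) | Halt in 4 levels: active only → literal | Added (points) |
|---|---|---|---|---|---|---|
| 2% | 0.059 | 0.096 | 2.4% → 3.9% | 1.5 | 1.4% → 2.2% | 1 |
| 5% | 0.143 | 0.226 | 13% → 21% | 7 | 8% → 12% | 4 |
| 10% | 0.271 | 0.410 | 41% → 56% | 15 | 26% → 38% | 11 |
| 20% | 0.488 | 0.672 | 85% → 94% | 9 | 66% → 80% | 13 |
| 30% | 0.657 | 0.832 | 98.1% → 99.6% | 1.5 | 90% → 96% | 6 |
| 40% | 0.784 | 0.922 | 99.9% → 100.0% | 0.1 | 98% → 99% | 2 |

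(Added points are from unrounded values.)

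**False MTD.** With no product effect, any declared MTD is spurious. After a halt at level k there are k − 1 lower doses to try, and each fails with probability q (q5 literal, q3 active only). The share of trials declaring an MTD within seven levels is the sum over k = 1 to 7 of (1 − h)^(k−1) × h × (1 − q^(k−1)).

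| p | Literal | Active only |
|---|---|---|
| 2% | 3% | 2% |
| 5% | 16% | 11% |
| 10% | 39% | 32% |
| 20% | 34% | 47% |
| 30% | 12% | 29% |

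The two cross at p of about 14%. Above that, active-only counting gives more spurious MTDs because lower doses clear more easily. Those declarations replace trials in which no lower dose would have cleared (at p = 20%, 60% literal against 38% active only).

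**The case against.** The best defence is that the active-only reading is what the sponsor means. The first trigger uses the word for group to mean the three exposed infants. In the repeat-group sentence, the remark about not escalating attaches to the dose of those three, and the placebo pair is listed separately. Placebo infants have no dose to hold or lower, and the MTD is a dose of *B. infantis*. A board that separates the arms at the first trigger has little reason to merge them later, and its procedures may be set out in documents that a condensed article does not show. Much of this stands: the fault is loose drafting of one rule, and it cannot be said that the sponsor chose to pool the arms. It does not remove the point, because the later sentences are written out in full and omit the restriction that the first one makes.

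The size is also open to challenge. It rests wholly on an assumed p. The added halt risk is material only in a middle band, roughly 5% to 20% over seven levels, and the article does not show that p lies there. That stands too.

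Two stronger readings are tempting. A reader might infer that a placebo event alone can stop escalation from the outset. It cannot, since an exposed infant at the same dose must have had an event first. A reader might also put the whole halt risk in the table down to this wording. The active-only values show that most of it comes from halting on any event in three infants, which is a safety choice and not questioned here.

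**Conclusion.** The point holds as a minor wording correction to a binding rule. The first trigger is limited to *B. infantis* infants; the repeat-group and de-escalation triggers, their all-clears and the MTD definition are not, and they refer to groups that include placebo infants. Read literally, after a first trigger in an exposed infant, a placebo-only event in the repeat group ends escalation permanently, and one in a de-escalated group forces a further step down.

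Assuming no product effect, independent infants and equal rates in both arms, the added chance of a permanent halt within seven levels peaks at about 15 points near p = 10% among the rates examined, and is about 1.5 points at p = 2% and p = 30%. Within four levels it is at most about 13 points at those rates. The documents do not support saying that the ED would be lost: that needs the literal reading to be applied, a background rate in the middle band, and an ED above the doses already given.

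**What to change.** Carry the first trigger's restriction through the rule:

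- repeat-group and de-escalation triggers: *at least one of the three infants receiving B. infantis*;
- all-clears: *none of the three infants receiving B. infantis*;
- MTD definition: the same population as the all-clears.

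Every event in an exposed infant still triggers, so no protection is lost. Optionally, show the board cumulative placebo events beside any repeat-group trigger, for information only: 10 placebo infants after a repeat group at level 4 (4 × 2 + 2) and 16 at level 7 (7 × 2 + 2), if no earlier level was repeated.

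The cost is a few words in a handful of sentences, with no extra infants or procedures. Trial status says that recruitment has not begun. The rewording removes only the placebo-driven part of false halts. If p exceeds about 14%, more trials would declare a spurious MTD, as the second table shows, in place of trials where no lower dose cleared. Any severity or relatedness threshold is for the sponsor and the board to decide and is not requested here.

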### Withdrawal of subjects

Subjects may be withdrawn without their consent if they acquire medical issues during the study period that require administration of oral or parenteral antibiotics or immunosuppressive medications. If a subject is to be withdrawn, the parent(s) will be contacted and the reason(s) for withdrawal will be explained in full. No further data will be collected from withdrawn subjects.

Subjects have the right to withdraw from the study at any time for any reason. Every effort will be made to follow-up subjects who discontinue placebo or *B. infantis* supplementation prior to the second dose. These evaluations should continue according to the protocol of scheduled study visits if at all possible. The reasons for discontinuation will be recorded in the subjects’ study file. If a subject is unable to return for evaluation, every effort will be made to contact via telephone 28 days after withdrawal to determine if any serious adverse events have occurred while off study. Any identified adverse events will be followed until resolution.

The investigator also has the right to remove subjects from the study without their consent. Possible reasons for removal include:Non-compliance with the study protocolSignificant protocol deviationSerious adverse event potentially related to study treatment

Subjects that withdraw after the 6 week study visit will not be replaced with new subjects.

## Discussion

From our experience of administering *B. infantis* to infants in the NICU at UC Davis, it is highly unlikely that a phase I trial will successfully identify a MTD of this probiotic. Thus, our proposed phase I ascending dose study will instead utilise a targeted outcome, optimal gut colonisation of *B. infantis* at 6 weeks of age. Such “concentration controlled” phase I clinical trials that use pharmacokinetics in place of drug toxicity to guide dose escalation are supported in the literature [23, 24]. For example, in molecularly targeted anticancer agents, toxicity concerns are reduced, making “drug-related biological effects” a better suited primary endpoint [25–28]. Our specific trial will measure gut microbiota composition following *B. infantis* administration to determine the dose of *B. infantis* that is required to successfully colonise the gastrointestinal tract of a 6-week-old breastfed infant. Secondary outcome measures will include measurement of complex glycan consumption by the infant as well as diversity of the intestinal microbiota. As in all phase I studies, the infants will be monitored closely for adverse events. The main goal of this phase I trial is to establish a recommended administering dose of *B. infantis* to support further efficacy testing in phase II and phase III trials.

Prior probiotic studies have differed from the proposed study with regards to their dosing regime, inclusion criteria, and types of bacteria administered. Many prior trials in infants were designed with limited knowledge of the human milk glycome and resultant effects on the infant’s intestinal microbiotia. Probiotic bacteria used in prior trials in children have included *Bifidobacterium breve*, *Bifidobacterium lactis*, *Bifidobacterium longum*, *Lactobacillus acidophilus*, *Lactobacillus fermentum*, and *Propinobacterium freudenreichii*, among others [29–34]. In many prior studies, it was unclear why a particular probiotic was chosen. Research done by the milk group at UC Davis has shown that the vast majority of probiotic species do not grow on the human milk oligosaccharides in breast milk [16, 35, 36]. Evidently, most probiotics studied in previous clinical trials have been selected based on culturability and taste profiles when administered as fermented food products rather than their biological activity. In contrast, our proposed study is based upon research into the human milk glycome and insight into the specific bacteria that digest breast milk oligosaccharides.

One unique aspect of this trial is that we will administer *B. infantis* to exclusively breastfed infants. The breast milk will provide the prebiotic oligosaccharides and thus select for the growth of *B. infantis* over other gastrointestinal commensal bacteria. In addition, we will monitor the composition of the intestinal microbiota should the mothers choose to discontinue breastfeeding to determine the effect breast milk consumption has on the maintenance of *B. infantis* intestinal colonisation. Previous studies investigating probiotics have administered the bacteria in combination with galacto- and fructo-oligosaccharides [37, 38]. However, these sugars differ significantly from milk oligosaccharides in that they are linear rather than branched and lack fucose and sialic acid moieties [39]. As human breast milk will comprise the majority of an infant’s diet, supplementing with a probiotic that thrives on human milk oligosaccharides may be the most sensible strategy for cultivating a protective microbiota in healthy infants.

The most common adverse effects described with probiotic use include diarrhoea, vomiting, and increased flatulence. Probiotics are known to be extremely safe, as evidenced by prior use in premature infants as well as in both adults and children with HIV [40, 41]. In Finland, the use of probiotic supplements (namely *Lactobacillus rhamnosous GG*) has increased dramatically over the past 20 years without evidence of a corresponding increase in the rate of lactobacillus bactermia [42, 43]. Probiotic supplementation has also been shown to be well tolerated without adverse effects in a recent randomised, double-blind, placebo-controlled trial comparing a combination of lactobacilli (*Lactobacillus salivarius* and *Lactobacillus paracasei*) and bifidobacteria (*Bifidobacterium animalis subsp. lactis* and *Bifidobacterium bifidum*) in pregnant women and infants, with the goal of assessing the safety of probiotic supplementation [44]. In this trial, enrolled women were treated with a total of 1 × 10^9^ colony-forming units of this probiotic regime daily for the last month of pregnancy and the regime was then administered to their infants from birth through to 6 months of age. There was no significant difference in the incidence of adverse events in either the maternal or infant groups, and no adverse events were attributed directly to the probiotic supplementation. There have been rare reports demonstrating the possibility of probiotic-related infectious complications, such as sepsis, bacteraemia, and endocarditis [45–47]. However, it is estimated that the risk of developing bacteraemia from ingested *Lactobacillus* probiotics is less than one in one million [48]. Though extremely rare, sepsis due to bifidobacterium has been described [49–51]. The described cases of bifidobacterium bacteraemia include one adult that developed incidental sepsis following acupuncture, and two infants that received *Bifidobacterium breve* or *Bifidobacterium longum* as a probiotic supplement. Of note, one infant was premature with extremely low birthweight and the other was full term with comorbid omphalocele. To date there are no reported instances of bacteraemia resulting from *B. infantis*; however, all study participants will be warned of the extremely low risk of such complications.

While studies have demonstrated the ability of certain probiotics to prevent childhood illnesses [8], there are virtually no data on how to appropriately dose these supplements. The typical probiotic study has adopted a daily dosing regime, making feasibility an issue. Sometimes the probiotic is administered to the mother first and then to the infant for the first 6 months of life. Dose-ranging studies are usually required early on during a drug’s clinical development. Excluding a few exceptions, probiotic dose-ranging studies are for the most part non-existent [52–54]. As a follow-up clinical trial, we plan to conduct a dose-ranging phase II study that will compare the effectiveness of *B. infantis* daily dosing to a limited dosing regime consisting of *B. infantis* administered on days 7 and 14 only. In theory, the human breast milk oligosaccharides will bestow *B. infantis* with a competitive growth advantage, making daily dosing unnecessary. If the limited dosing regime is successful, it will have an immediate health care impact, as inoculating breast fed infants with two doses of *B. infantis* is an extremely feasible preventative measure to reduce the incidence of atopy and other diseases in at-risk children.

The pharmacokinetically guided design of this proposed phase I trial has not been attempted in prior probiotic studies. If successful the trial will identify a pharmacologically effective dose (ED) and maximum effective dose (MaxED) for *B. infantis* supplementation in healthy infants. The next generation sequencing strategy that will be employed to analyse the stool of the infants to determine gut colonisation with *B. infantis* has been well standardised, and is a common method for analysis of gut microbiota. Infants will also be monitored closely for potential adverse effects in case a maximally tolerated dose (MTD) is reached during the ascending dose study. The design of the trial is also innovative because the specific probiotic used for the supplementation will have a competitive advantage in an exclusively breastfed infant; it is the only bacterium that can fully utilise the complex oligosaccharides in breast milk as an energy source. Thus, the design of the trial provides an optimal environment for *B. infantis* to outcompete other intestinal microbiota. The rationale for the choice of probiotic used in prior infant trials is not clear; however, in this study it is based upon knowledge of the human milk glycome and specific metabolic needs of *B. infantis*. Our ultimate goal is to develop a clinically appropriate, safe, and effective dosing regime for probiotics that may be utilised in further phase II and phase III clinical trials. In doing so, we hope to lay the foundation for the design of objective, standardised clinical trials to assess the efficacy of probiotics for the prevention of a variety of diseases, including atopic dermatitis and food allergies in at-risk infants.

